### Planned data analysis

REDCap, a secure web application, will be used as the primary data tracking, data collection, and data management platform for all assessments. Quantitative data analyses will be conducted only on participants recruited during Phase 3 (i.e., once random assignment has begun). As a first step, the equivalence of treatment conditions with regard to key baseline variables will be assessed. This will involve comparisons of treatment conditions on demographic characteristics and baseline levels of potential treatment moderators. Should conditions differ on any characteristic, these variables will be placed in models as interactions with group assignment along with its main effect and also in a distinct model with the interaction removed. The model with the lowest AIC will be retained. Other preliminary analyses will include studies of patterns of missing data, research dropout rates, distributional properties of dependent and other measures, and correlations among outcomes measures.

Data analysis will follow a sequence designed to examine the primary outcome questions: (1) Does MI-NAV lead to higher rates of linkage to community-based PrEP care? (2) Does MI-NAV lead to better PrEP adherence, based on dried blood spot tests (DBS), compared to SOC? (3) Does MI-NAV lead to better retention in care compared to SOC? There is little expectation of observed HIV seroconversion, given the modest sample size and 6-month follow-up window. However, seroconversion rates of each condition will be examined. Analyses will also be conducted to examine the relative impact of MI-NAV versus SOC on self-reported PrEP adherence. Following the intention-to-treat principle, all randomized participants will be included in the analyses. We anticipate an attrition rate less than 10%, which will provide us with a final sample size of at least 54 participants in the MI-NAV condition and 18 participants in the SOC condition. This estimate is based on previous research with a high-risk, incarcerated population, in a geographically similar setting, which retained 96% of participants at 12-month follow-up [54]. In addition, we will employ retention strategies that increase retention rates in this population [55], including: (1) offering interview incentives that are higher than normal hourly rates of pay and providing transportation to and from interview locations; (2) conducting regular phone check-ins or sending letters between appointments to ensure contact information has not changed; (3) collecting contact information of secondary contacts, such as friends or relatives, that will know how to reach the participant; and 4) working with local criminal justice agencies, parole officers, and police departments that can help maintain or reestablish contact with participants if necessary.

Given that this is a pilot study, the primary goal is to yield a stable estimate of the effect size rather than to find statistically significant differences. The effect size estimate will be useful in planning a future RCT. We are aware of the dangers of relying exclusively on small pilot studies to gauge the promise of interventions [56]. These effect size estimates have a large standard error, and we primarily will be hoping to find a pattern of results that is supportive of MI-NAV, at which point a full scale trial will be designed to test for a clinically meaningful effect size. To provide stable odds ratios for estimates of effect size for dichotomous or categorical variables, such as PrEP care linkage, a somewhat larger sample size is required. For continuous variables, group means typically begin to stabilize around 15 participants per group. We believe that the sample size of 60 participants in MI-NAV and 20 participants in SOC, even after attrition, will allow us to evaluate the potential of MI-NAV to improve PrEP linkage while maximizing the number of participants in the MI-NAV condition in order to fully assess the feasibility and acceptability of the intervention.

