#### Phase 3: pilot RCT

For the pilot RCT, 80 participants will be recruited and assigned to a condition using a 3:1 ratio, with 60 participants assigned to MI-NAV and 20 participants assigned to SOC. Participants in the SOC condition will also meet with a study interventionist twice while incarcerated. During the first session, SOC participants will receive a pamphlet regarding PrEP during incarceration and will be informed that they can initiate PrEP by speaking with a provider from the correctional facility. Mirroring MI-NAV, the second session will occur 2 weeks before the participant is released from incarceration. This session will involve a referral to community-based PrEP care if the participant is interested and referral to community-based SUD treatment when appropriate. Participants will be randomly assigned to condition using urn randomization; the urn blocking variable will be baseline level of HIV risk behavior as assessed by the HIV Risk Assessment Battery (RAB) [42]. The 3:1 randomization ratio will allow us to maximize the information gained about the MI-NAV intervention while including a comparison condition. RCT participants will complete a baseline interview while incarcerated and follow-up interviews at 1, 3, and 6 months post-release from incarceration. Baseline and follow-up interviews will be conducted by research assistants who will be blind to participants’ assigned condition. RCT participants will receive gift cards in the amount of $25, $30, and $50, respectively, for the 1-, 3-, and 6-month follow-ups (see Table 1 for timing of Phase 3 protocol elements). No compensation will be provided for the baseline interview or sessions/check-ins with the interventionist.

**Table 1 Tab1:** Timing of participant enrollment, receipt of intervention, and assessment activities during Phase 3

Timepoint	Enrollment	Baseline	Post-allocation		
	− t1	0	+ 1 month	+ 3 months	+ 6 months
Enrollment					
Eligibility screen	X				
Informed consent	X				
Allocation		X			
Interventions					
MI-NAV					
SOC		X			
Assessments					
Primary outcomes			X	X	X
Secondary outcomes			X	X	X
Other outcomes		X	X	X	X

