##### PrEP care initiation and linkage to care

Information will be extracted from participants’ medical records at the correctional facility regarding whether PrEP was prescribed and whether PrEP was administered each day during the period of incarceration. Linkage to community-based PrEP care is operationalized as receipt of a prescription for PrEP from a community-based provider within 3 months of release from incarceration, verified through medical record data extraction. This time window was selected because it is consistent with the CDC’s guidelines for PrEP follow-up visits (every 3 months) [38].

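### The pilot's primary goal is a stable effect size, but 60 versus 20 women cannot give a stable odds ratio for linkage at any linkage rates

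*Protocol article*

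**What the plan says.** Under Planned data analysis, the article sets the purpose of the sample: "the primary goal is to yield a stable estimate of the effect size rather than to find statistically significant differences". It adds that the estimate will help to plan a later RCT. The same paragraph then says "These effect size estimates have a large standard error" and, of odds ratios for dichotomous outcomes, "such as PrEP care linkage, a somewhat larger sample size is required". No number is attached to that requirement. The only benchmark, about 15 per group, concerns means of continuous variables. The paragraph closes with the authors' belief that 60 and 20, even after attrition, will let them evaluate the potential of MI-NAV for linkage. Attrition below 10% is expected to leave "at least 54 participants in the MI-NAV condition and 18 participants in the SOC condition".

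The primary outcome is binary: "receipt of a prescription for PrEP from a community-based provider within 3 months of release from incarceration", taken from medical records (PrEP care initiation and linkage to care). Primary RCT analyses assigns it to a fractional logit model fitted by GEE. The article gives no linkage rate, target odds ratio or interval width.

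**The concern.** A goal of stability is a claim about precision, and here it carries the justification for 80 women. The paragraph offers no precision figure for linkage and itself describes the estimates as imprecise. A reader who takes the stated goal at face value could give the pilot odds ratio more weight in planning than it can bear.

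A second, conditional problem follows from the effect measure. The SOC arm is small. If few SOC women link, the count in that cell may be zero, and an ordinary logit fit then has no finite odds ratio. The printed output may not make this obvious.

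**Working it through.** **The plan's own figures.** 80 × 0.75 = 60 and 80 × 0.25 = 20. After 10% attrition, 60 × 0.9 = 54 and 20 × 0.9 = 18. These reproduce exactly. N = 80 has no precision or power calculation to reproduce.

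**Inputs.** Arm sizes are from Phase 3: pilot RCT and Planned data analysis. Linkage rates are not given, so those below are assumptions. Intervals are 95% two-sided, at expected counts.

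**Formula.** SE(log OR) = √(1/a + 1/b + 1/c + 1/d), where a and b are linked and not linked in MI-NAV, and c and d the same in SOC. Ratio of upper to lower limit = exp(2 × 1.96 × SE).

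**Floor at any rates.** The SE is smallest when both arms are at 50%.
- 60/20: SE = √(1/30 + 1/30 + 1/10 + 1/10) = √0.2667 = 0.516; ratio 7.6 (OR 1.00, 0.36 to 2.75). The SOC arm supplies 0.2000 of the 0.2667, or 75% of the variance.
- 54/18: SE = √(1/27 + 1/27 + 1/9 + 1/9) = √0.2963 = 0.544; ratio 8.4.

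**Assumed rates.**

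| SOC / MI-NAV | OR | 60/20: 95% CI (ratio) | 54/18: 95% CI (ratio) |
|---|---|---|---|
| 30% / 50% | 2.33 | 0.79–6.88 (8.7) | 0.75–7.30 (9.8) |
| 25% / 50% | 3.00 | 0.97–9.30 (9.6) | 0.91–9.89 (10.9) |
| 20% / 40% | 2.67 | 0.79–8.95 (11.3) | 0.74–9.56 (12.9) |
| 10% / 30% | 3.86 | 0.81–18.39 (22.7) | 0.74–20.0 (26.9) |
| 5% / 20% | 4.75 | 0.58–39.1 (68) | 0.52–43.8 (85) |

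Example, 25% / 50% at 60/20: SE = √(1/30 + 1/30 + 1/5 + 1/15) = 0.577.

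**Risk difference, 30/60 versus 5/20.** Wilson limits are 0.377 to 0.623 for MI-NAV and 0.112 to 0.469 for SOC. Newcombe lower limit = 0.25 − √[(0.500 − 0.377)² + (0.469 − 0.250)²] ≈ −0.001. Upper limit = 0.25 + √[(0.623 − 0.500)² + (0.250 − 0.112)²] ≈ 0.435. The interval is therefore about −0.1 to 43 points. At 54/18 it is about −1 to 44 points, though that case implies 4.5 SOC events, which is not a possible count.

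**Chance of no SOC linkage**, (1 − p)ⁿ with n = 20 (n = 18):
- p = 5%: 36% (40%)
- p = 10%: 12% (15%)
- p = 15%: 3.9% (5.4%)
- p = 20%: 1.2% (1.8%)
- p = 25%: 0.3% (0.6%)

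**What the model does then.** A binomial-logit GEE fitted to 20/60 versus 0/20 linkages returned a log OR of 23.9 with a robust SE of 0.27, and the software reported convergence. The estimate is an artefact of where the iterations stopped, and the SE makes it look precise.

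**Allocation is not the remedy.** At 20% / 40%, 40/40 still gives 0.98 to 7.25, a ratio of 7.4. A ratio of 4 would need about 248 analysed women at 3:1, or 168 at 1:1.

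**The case against.** The strongest reply is that the imprecision is disclosed. The paragraph admits the large standard error, warns against relying exclusively on small pilots, hopes mainly for a supportive pattern, and says a full trial will be designed around a clinically meaningful effect. The Discussion adds that significance is unlikely. This stands as far as it goes: the reader is not kept in the dark, and it would be wrong to infer that the next trial will simply be sized on the pilot odds ratio. But the disclosure contradicts the stated goal without withdrawing it.

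The remark about needing a larger sample is ambiguous. It may explain why the arms exceed 15, and need not admit that 60 and 20 are too few. The closing sentence claims only that the potential of MI-NAV can be evaluated. Both readings are fair. The precision result depends on neither.

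A reader might also infer that the odds ratio will probably not exist or that the model will not converge. The documents do not support this. No SOC rate is given. General statements about barriers suggest low linkage, but SOC women get two meetings, a pamphlet and, if interested, a referral. The ten-fold width and a material zero-cell risk also belong to different assumed rates. And the fit shown above reported convergence: the defect is an infinite estimate with a meaningless standard error.

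Finally, 54 and 18 may not apply to linkage. It comes from medical records, permission will be sought to use records for women who miss follow-up, and the main analysis includes everyone randomized. So 60 and 20 is the better base case. Low power is no error, since no significance target is set. A sparse-data fallback commonly sits in an analysis plan that is not shown, so its absence here is not itself the finding.

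**Conclusion.** The point holds as a mismatch between the stated primary goal and what the design gives for the primary outcome. The floors of 7.6-fold (60/20) and 8.4-fold (54/18) require no assumption about linkage rates. The wider figures, roughly 9- to 13-fold at SOC rates of 20 to 30% and over 20-fold at 10% or below, rest on assumed rates. The zero-cell problem is conditional: a 12 to 40% chance at true SOC rates of 5 to 10%, negligible from about 25%. The design itself need not change. The claim should, and the odds ratio for linkage needs a method that survives an empty cell.

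**What to change.** - Replace the goal of a stable estimate with the expected precision over a stated range of linkage rates, labelled as assumptions. For example, at 60/20 and 50% versus 25%: OR 3.0 (95% CI 0.97 to 9.3) and risk difference 25 points (about −0.1 to 43). Give 54/18 as the attrition case.
- Report each arm's linkage rate and the unadjusted risk difference with score (Wilson and Newcombe) intervals, beside the planned adjusted model. These remain defined with an empty cell; they do not add information.
- Use Firth-penalized logistic regression for the linkage odds ratio, which has a single time point. GEE can stay for the repeated outcomes.
- Keep the sentence on a clinically meaningful effect in the full trial, and qualify the one on usefulness for planning: the pilot odds ratio will not by itself set that trial's size.

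The cost is some rewording and slightly more analysis work, with no further participants. The stated claim becomes less favourable.

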#### Primary RCT analyses

Tests of the effects of treatment on the primary outcome variable (linkage to community-based PrEP care) and secondary outcomes (PrEP DBS adherence and retention in care at 3 and 6 months) will be conducted using a fractional logit model [57] estimated by Generalized Estimating Equations (GEE) [58–60]. GEE is a quasi-likelihood estimation method of repeated measures analysis for appropriate modeling of covariance structures when outcomes are correlated across time. Additionally, it allows for the inclusion of both categorical and continuous independent variables. While it is most common to use logistic regression to analyze dichotomous variables, the fractional logit model can be used for any fractional outcome with a range of 0–1. An advantage of GEE over ANOVA is that GEE models nesting by adjusting the standard errors of the test statistics based on the covariances (and variances) of nested observations, rather than depending on calculating differences. These variances and covariances can be modeled based on all data available. Therefore, a subject with missing data for one time point will not contribute to the variance or covariance estimates involving that time point, but their non-missing time points will be used to estimate those variances and covariances.

The primary, between groups, independent variable in the above GEE is treatment group. Variables measured at baseline will be examined using screening runs prior to primary analyses to see which of these baseline measures are most strongly associated with the outcomes (linkage to PrEP, PrEP DBS adherence, retention in PrEP care, and self-reported adherence). Those that show significant relationships with outcome will be entered as covariates in the primary analyses unless there are concerns over multicollinearity. The linear effect of time will also be included as a covariate in these analyses, as we assume that retention and adherence rates will show a tendency to decrease over time. We will also test for non-linear (i.e., linear plus quadratic) effects of time for the repeated measures, adherence and retention. Testing the time by group interaction will indicate the extent to which treatment differences are more or less pronounced over time.

Analyses will be conducted separately on two overlapping samples. Following the intention-to-treat principle, all randomized participants will be included in the first set of analyses. This is the most conservative approach and represents our main outcome analysis. Analyses will also be conducted on subjects who completed the assigned intervention, the “as-treated” analysis. Although subject to more bias, especially if attrition rates are high, this latter approach answers more directly the question of intervention efficacy by providing an estimate of the maximal effects attained by an intervention. Similar results with both approaches increases confidence in the findings.

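### Baseline RAB is the urn randomization variable, but whether it enters the primary model, and so which odds ratio is reported, is left to the data

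*Protocol article*

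**What the plan says.** Protocol article, Phase 3: pilot RCT: "80 participants will be recruited and assigned to a condition using a 3:1 ratio, with 60 participants assigned to MI-NAV" and the other 20 to SOC. On the method of assignment, "the urn blocking variable will be baseline level of HIV risk behavior as assessed by the HIV Risk Assessment Battery (RAB". No other balancing variable is named.

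Protocol article, Primary RCT analyses, fixes two terms in the GEE model. The first is treatment: "The primary, between groups, independent variable in the above GEE is treatment group". The second is time: "The linear effect of time will also be included as a covariate in these analyses". Other covariates are chosen from the data: "Variables measured at baseline will be examined using screening runs prior to primary analyses", against linkage, dried-blood-spot adherence, retention and self-reported adherence. The entry rule is: "Those that show significant relationships with outcome will be entered as covariates in the primary analyses unless there are concerns over multicollinearity". RAB is not exempted, and no criterion is given for a multicollinearity concern.

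Protocol article, Planned data analysis, gives a second way in. Arms are compared at baseline on demographics and potential moderators, and RAB is listed among the moderators. A variable on which the arms differ enters as a main effect, with and without an interaction with group, and AIC chooses between the two models.

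**The concern.** An analysis normally carries the variables used to balance the randomization, whether or not they turn out significant, so that it reflects how participants were assigned. Here the design gives RAB a special role and the analysis gives it none.

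This bears on the study's stated goal, which is a stable effect-size estimate for planning a later trial. The planned model is a logit model, and odds ratios are non-collapsible: the odds ratio conditional on a prognostic covariate differs from the one that ignores it, even with perfect balance. If the data decide whether RAB is in the model, a planner cannot know beforehand which of the two quantities the pilot will deliver.

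**Working it through.** **1. The plan's own figures.** Allocation: 80 × 3/4 = 60 and 80 × 1/4 = 20. The plan states "We anticipate an attrition rate less than 10" percent, and 60 × 0.90 = 54 and 20 × 0.90 = 18. This reproduces the stated "final sample size of at least 54 participants in the MI-NAV condition and 18 participants in the SOC condition". These figures are not in dispute.

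**2. Ways for RAB to enter the primary model.**
- Fixed terms: treatment and time. RAB is not among them.
- Screen: RAB enters if significantly related to outcome. It can still be left out for multicollinearity, and timeline-followback HIV risk behavior is collected at the same baseline visit.
- Baseline imbalance: RAB enters if the arms differ on it. Urn balancing on RAB makes this unlikely. If it did happen, AIC would then decide whether an interaction stays.

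Both available ways depend on the data, so neither secures RAB a place.

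**3. How often the screen admits RAB.** All inputs here are assumptions: 80 women at 60:20, a two-sided 0.05 screen, and logistic models for binary linkage.

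*Continuous RAB.* SOC linkage is 25% and MI-NAV linkage 50% at mean RAB, so the treatment odds ratio is (0.50/0.50)/(0.25/0.75) = 3. Repeated simulations agree closely:
- log odds ratio 0.3 per SD: RAB admitted in 20–24% of trials
- 0.5 per SD: 49–52%
- 0.8 per SD: 86–87%

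*Two RAB strata of 40.* Allocation is balanced within strata, with 3,000 runs per setting and SOC linkage of about 20% or 35% midway between the strata. RAB is admitted in 10–14% of trials if its odds ratio is 1.5, 20–32% if 2, 47–67% if 3, 67–84% if 4, and 87–97% if 6.

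**4. What it does to the estimate and the test.** Two-strata setting, true conditional treatment odds ratio 3; each cell gives RAB omitted / always included / screened:

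| SOC linkage | RAB OR | Median treatment OR | Power |
|---|---|---|---|
| 20% | 2 | 3.06 / 3.21 / 3.12 | 0.40 / 0.43 / 0.42 |
| 20% | 3 | 2.86 / 3.14 / 3.12 | 0.37 / 0.42 / 0.42 |
| 35% | 2 | 2.99 / 3.09 / 3.05 | 0.52 / 0.53 / 0.53 |
| 35% | 3 | 2.85 / 3.19 / 3.15 | 0.49 / 0.53 / 0.53 |
| 35% | 6 | 2.49 / 3.13 / 3.11 | 0.39 / 0.46 / 0.46 |

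Null rejection at nominal 0.05 is 0.025–0.041 with RAB omitted, 0.027–0.046 always included and 0.027–0.044 screened.

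For continuous RAB at 0.5 per SD, the median odds ratio is about 3.0 omitted and 3.2 included (2.86 and 3.12 in another run). The median standard error of the log odds ratio is 0.578 omitted and 0.596 included.

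**5. Scale of the shift.** ln(3.2/3.0) = 0.065, and 0.065/0.578 = 0.11 standard errors. In the run with 2.86 and 3.12, ln(3.12/2.86) = 0.087, or 0.15 standard errors.

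**The case against.** The strongest reply is that the protocol screens RAB rather than omitting it, and a screen drops RAB mainly when RAB hardly predicts outcome in that sample. This stands. In screened-out trials the median odds ratio was about 3.05 unadjusted against 3.13–3.23 adjusted, so the frequency with which RAB is dropped is not a measure of damage. It also stands that the imbalance rule would catch RAB if the urn left it clearly unbalanced, so the significance screen is not the only way in.

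A reader might infer that leaving RAB out makes the error bars too wide and wastes precision. That is linear-model reasoning. In a logit model, adding a prognostic covariate raises the standard error of the treatment log odds ratio (0.578 to 0.596 above). The small power gain comes from the conditional odds ratio lying further from 1. An unadjusted standard error can be conservative after balanced allocation, but this became visible only with a very strong RAB effect (log odds ratio 1.2 per SD: standard error 0.577 against a true spread of 0.554).

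A reader might also want one covariate list for every outcome. The documents give no ground for requiring it: linkage is binary, dried-blood-spot concentration is continuous and taken only from women prescribed PrEP, and retention is visit attendance. Their prognostic covariates may reasonably differ.

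A last reply is that such detail belongs in an analysis plan that is not shown. It does not stand, because the article states an explicit selection rule for the primary analysis and RAB falls under it.

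**Conclusion.** The point holds as a mismatch between design and analysis. RAB is the randomization variable, and nothing in the stated rules guarantees it a place in the primary model. The data therefore settle whether the reported odds ratio is conditional on RAB.

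The numerical effect is modest. With a moderately prognostic RAB, inclusion is close to a coin toss, but the estimate moves by only about 0.1 to 0.15 of a standard error. Screened power is within about 0.02 of always adjusting. The simulations show no type I inflation, so an inference that the screen invalidates the test is not supported. The gap between omitting and including RAB becomes large (2.49 against 3.13) only when RAB is very strongly prognostic, and then the screen admits it in about 97% of trials.

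Every simulated figure rests on assumed linkage rates, RAB effects and a 0.05 screening level, none of which the documents give. The textual finding does not depend on them. For a pilot that aims at effect-size estimation and expects large standard errors, the reason to change is clarity about what is estimated, at almost no cost.

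**What to change.** In Primary RCT analyses, state that baseline RAB, in the form used in the urn, is a fixed covariate in the primary and secondary models regardless of the screening result, the baseline comparison or any multicollinearity concern. If another risk measure is collinear with RAB, that measure should be the one left out. Name any further covariates before outcome data are examined; they may differ by outcome.

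Cost: one sentence, and one degree of freedom if RAB enters as a single term. RAB is already collected at baseline, and trial conduct does not change.
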